## Abstract

**Background:**

Despite recent advances in acute stroke treatment, basilar artery occlusion (BAO) is associated with a death or disability rate of close to 70%. Randomised trials have shown the safety and efficacy of intravenous thrombolysis (IVT) given within 4.5 h and have shown promising results of intra-arterial thrombolysis given within 6 h of symptom onset of acute ischaemic stroke, but these results do not directly apply to patients with an acute BAO because only few, if any, of these patients were included in randomised acute stroke trials.

Recently the results of the Basilar Artery International Cooperation Study (BASICS), a prospective registry of patients with acute symptomatic BAO challenged the often-held assumption that intra-arterial treatment (IAT) is superior to IVT. Our observations in the BASICS registry underscore that we continue to lack a proven treatment modality for patients with an acute BAO and that current clinical practice varies widely.

**Design:**

BASICS is a randomised controlled, multicentre, open label, phase III intervention trial with blinded outcome assessment, investigating the efficacy and safety of additional IAT after IVT in patients with BAO. The trial targets to include 750 patients, aged 18 to 85 years, with CT angiography or MR angiography confirmed BAO treated with IVT. Patients will be randomised between additional IAT followed by optimal medical care versus optimal medical care alone. IVT has to be initiated within 4.5 h from estimated time of BAO and IAT within 6 h. The primary outcome parameter will be favourable outcome at day 90 defined as a modified Rankin Scale score of 0–3.

**Discussion:**

The BASICS registry was observational and has all the limitations of a non-randomised study. As the IAT approach becomes increasingly available and frequently utilised an adequately powered randomised controlled phase III trial investigating the added value of this therapy in patients with an acute symptomatic BAO is needed (clinicaltrials.gov: NCT01717755).

## Background

Stroke is the leading cause of disability in developed countries [1]. Posterior circulation stroke accounts for about 20% of all ischaemic strokes. The basilar artery is the main vessel of the posterior circulation that supplies most of the brainstem and occipital lobes, and part of the cerebellum and thalami. Basilar artery occlusion (BAO) can cause many symptoms such as isolated cranial nerve palsies or hemiplegia, but also a locked-in state or coma. Despite recent advances in acute stroke treatment BAO is associated with death or disability rate of close to 70% [2].

Randomised trials have shown the safety and efficacy of intravenous thrombolysis given within 4.5 h and promising results of intra-arterial thrombolysis given within 6 h of symptom onset of acute ischaemic stroke [3-8]. Unfortunately these results do not directly apply to patients with an acute BAO because only few, if any, of these patients were included in randomised acute stroke trials. As yet, BAO has not been studied in isolation in randomised clinical trials. Patients with BAO only represent about 5% of all thrombolysed stroke patients [9,10]. We are aware of only one attempt to perform a randomised treatment trial in patients with an acute BAO, which was terminated prematurely because of poor recruitment [11]. Case series of patients with BAO found similar outcomes in patients treated with antithrombotic therapy, intravenous thrombolysis (IVT) or intra-arterial treatment (IAT) [11,12].

Recently our study group reported the results of the BASICS registry, a prospective registry of patients with an acute BAO [2]. We were not able to identify a statistically significant superior treatment strategy. However the inclusion of >600 patients in the registry over a 5-year period suggests that the performance of a randomised trial in patients with BAO is feasible.

Our observations in the BASICS registry underscore that we continue to lack a proven treatment modality for patients with an acute BAO and that current clinical practice varies widely. Furthermore, the often-held assumption that IAT is superior to IVT in patients with an acute symptomatic BAO is challenged by our data. Although recanalisation rates are consistently higher after IAT as compared to IVT in observational studies, this was not consistently accompanied by improved outcome [13,14].

The BASICS registry was observational and has all the limitations of a non-randomised study. Reasons for clinicians to select a specific treatment option are more complex than can be captured in the scope of a prospective registry. Multivariable analyses can never adjust completely for systematic differences between treatment groups. A bias towards a more aggressive treatment approach in patients who were thought to have a worse prognosis may have influenced the outcome in the IAT group and relinquishing both IVT and IAT in patients with a severe deficit may have been an expression of a more palliative approach. Crossover to another treatment group because of clinical worsening or lack of treatment response was not taken into account. There may have been unmeasured variables relevant to outcome that were imbalanced between groups.

As the IAT approach becomes increasingly available and frequently utilized an adequately powered large randomised controlled phase III trial investigating the added value of this therapy in patients with an acute symptomatic BAO is needed.

## Methods

BASICS is a multicentre, open label, randomised, controlled, phase III trial comparing optimal medical care with best intra-arterial therapy in patients with BAO who were treated with intravenous thrombolysis. A total of 750 patients will be included. Follow-up will continue until 1 year after inclusion of the last patient.

### Enrollment criteria

Patients can be enrolled in the study if the following criteria have been met:

1. symptoms and signs compatible with ischaemia in the basilar artery territory and an National Institutes of Health Stroke Scale (NIHSS) ≥10 at time of randomisation;

2. BAO confirmed by CTA or MRA;

3. aged 18 to 85 years;

4. initiation of IV rt-PA within 4.5 h of estimated time of BAO. Estimated time of BAO is defined as time of onset of acute symptoms consistent with the clinical diagnosis of basilar artery occlusion or if not known last time patient was seen normal prior to onset of these symptoms, hence time from symptom onset can be considerably longer than 4.5 h;

5. initiation of IA therapy should be feasible within 6 h of estimated time of BAO;

6. informed consent.

Patients will be excluded from the study in case of:

1. pre-existing dependency with a modified Rankin scale (mRS) ≥3;

2. female of childbearing potential who is known to be pregnant or lactating or who has a positive pregnancy test on admission;

3. need for haemodialysis or peritoneal dialysis;

4. other serious, advanced or terminal illness;

5. any other condition that the investigator feels would pose a significant hazard to the patient if IA therapy is initiated;

6. current participation in another research drug treatment protocol (patient cannot start another experimental agent until after 90 days);

7. lesion consistent with haemorrhage of any degree on neuroimaging;

8. significant cerebellar mass effect or acute hydrocephalus on neuroimaging;

9. bilateral extended brainstem ischaemia on neuroimaging.

### Study procedures

Based on the experience in the BASICS registry an estimated 40% to 50% of patients will present in community hospitals with subsequent referral to an intervention centre. Community hospitals should be encouraged to initiate IVT prior to transfer according to the ‘drip and ship’ principle. Intubation prior to transfer should be strongly encouraged in any subject deemed unstable or at high risk of aspiration. If sedation is needed, short acting drugs, like propofol (di-isopropylfenol) should be given to avoid interference with the neurological examination upon arrival at the intervention centre. A diagnostic neuroimaging screening with CT/CTA or MRI/MRA confirming the presence of BAO and the absence of imaging exclusion criteria, and a NIHSS of 10 or more will be used to identify patients eligible for the trial.

In case of an increase in NIHSS by ≥5 points during transfer and in any comatose subject a repeat CT scan of the brain should be performed prior to randomisation to exclude intracranial hemorrhage. In those patients in whom BAO is assessed prior to transfer a repeat CTA should be performed prior to randomisation in the intervention centre to reassess basilar artery patency in case of an improvement in NIHSS by ≥5 points during transfer or a time delay beyond 2 h after initial confirmation of BAO and in any comatose subject.

### Randomisation

After obtaining informed consent patients will be randomised into one of the two treatment arms. Patients are randomised by a secure link to a central randomisation database. Randomisation will be stratified for stroke severity (NIHSS score <20 versus ≥20), for centre and for time of symptom onset (within 4.5 h of symptom onset versus beyond 4.5 h of symptom onset, but within 4.5 h of estimated time of BAO).

### Registry of patients with BAO who are not randomised

To evaluate a possible selection bias of patients included in the trial, participating centres are obliged to enter all patients with acute symptomatic BAO presenting at their centre who are treated with IVT or IAT but who are not randomised, in a registry. Data are collected on patient characteristics, time to treatment, eligibility, reason for non-inclusion and type of treatment.

### Treatment

One of the guiding principles of the BASICS trial is rapid initiation of thrombolytic therapy to an eligible subject to provide maximal benefit. To minimize any delay in the administration of a proven effective therapy (that is, IV rt-PA), the standard dose of open-label IV rt-PA (0.9 mg/kg; 90 mg maximum) is initiated prior to enrolment and randomisation in the trial if standard eligibility criteria are met.

Patients treated with IVT within 4.5 h of first symptom onset, and those who are treated beyond 4.5 h of first symptom onset, but within 4.5 h of estimated time of BAO, will be regarded as two pre-specified subgroups for secondary analysis. In patients treated beyond 4.5 h of symptom onset, informed consent needs to be obtained prior to initiation of IVT.

IA therapy has to be initiated within 6 h of estimated time of BAO. Endovascular treatment will be performed by an experienced interventional radiologist with a track record of at least 10 intra-arterial interventions both in the middle cerebral and basilar artery in the last 2 years. If an appropriate thrombus or residual stenosis is identified, the choice of IA strategy will be made by the treating neurointerventionalist.

### Objectives

The primary objective of the trial is to evaluate the efficacy of additional IAT in patients with BAO treated with IVT, in terms of favourable outcome at 90 days, defined as a modified Rankin score of 0–3.

Secondary analysis will compare outcome in the following pre-defined subgroups: patients with a baseline NIHSS of 10–19, and those with a baseline NIHSS of ≥20.

Patients treated with IVT within 4.5 h of first symptom onset, and those treated beyond 4.5 h of first symptom onset within 4.5 h of estimated time of BAO.

Secondary objectives are safety evaluation of a combined IV/IA approach compared with IV rt-PA alone, evaluation of the safety and efficacy of mechanical devices as part of a combined IV/IA approach and evaluation of efficacy of a combined IV/IA approach compared with IV rt-PA alone in terms of a favourable outcome on other clinical and radiological measures. Other clinical and radiological measures for evaluation of efficacy will be: (1) Excellent outcome defined as a mRS of 0–2 at day 90 and 1 year; (2) mRS - not dichotomized at day 90 and 1 year; (3) EQ-5D at day 90 and 1 year; (4) an improved early response to treatment as determined by a reduction in NIHSS by 5 points or more at 24 h; (5) a CT or MR angiography assessment of basilar artery patency at 24 h, and (6) the extent of cerebral infarction as measured by the pc-ASPECTS score on NCCT (non-contrast CT) or MRI at 24 h. The primary measures for evaluation of safety will be symptomatic intracranial haemorrhage or intracranial haemorrhage contributing to patients’ death as determined by the study safety committee confirmed on neuroimaging within 3 days of treatment initiation (CT or MRI), or overall mortality at 90 days.

### Follow-up

Length of follow-up will be 1 year with a blinded exam at day 90 (mRS, EQ-5D) and telephone surveys at 30 days (mRS) and 1 year (mRS, EQ-5D).

### Statistical considerations

#### Power calculation

Assuming an absolute increase of 10% of favourable outcome at 90 days by additional IA therapy compared to optimal medical care alone, we calculated that 712 patients would be needed. This calculation was based on a type 1 error of 5%, a type 2 error of 20%, and a presumed incidence of the primary outcome event of 30% in the group treated with optimal medical care. This latter incidence was based on data of the BASICS registry study [2]. Based on these assumptions the trial would yield a risk ratio of 1.33 with a 95% confidence interval of 1.09 to 1.63, that is, a relative increase of 33% more patients with a favourable outcome with additional IA therapy. The sample size formula used originated from the standard work on clinical trials by SJ Pocock [15]. To account for potential dropout a target of 750 patients was set.

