### Monitoring

An independent DSMB will monitor the trial. For efficacy a symmetrical two-sided stopping rule will be used. The size of the trial is based on the assumption of a 10% absolute increase of the proportion of patients with a favourable outcome treated with additional IA therapy as compared with optimal medical care alone. If the observed benefit is ‘clearly’ larger or if optimal medical care appears to be better than additional IA therapy early termination of the trial may be recommended. A restricted procedure will be used with alpha equal to 0.05 and a power of 0.80 [16].

Safety will be monitored as follows. The BASICS registry observed that the risk of symptomatic intracranial haemorrhage (sICH) in patients treated with IA therapy was 14% (95% CI 10-18%) and 7% (95%CI 3-11%) in those treated with IVT only [2]. A more than two-fold excess of symptomatic intracranial haemorrhage in the group treated with additional IA therapy as compared with maximum supportive treatment may therefore be considered as problematic. However, symptomatic intracranial haemorrhage is a contributing component of the primary outcome and hence is weighed during monitoring of this outcome. A higher than expected sICH rate in the absence of a significant difference in functional outcome may therefore lead to a decision to put the trial on hold to analyse the reason for this higher sICH rate and the need to change treatment recommendations such a adjustments in the dose of thrombolytics used or the use of specific devises.

The BASICS Trial Office will put an active follow-up system into effect, such that for each patient 90-day follow-up data and those on the occurrence of symptomatic intracranial haemorrhage are obtained without delay. The first interim analysis will be performed at the moment the 3-month follow-up data are available on the first 10 patients randomised. Every 4 months thereafter the DSMB will be given the latest follow-up data and will advise the steering committee about the continuation of the trial based on these data. Thus a sequential monitoring process is installed based on the procedures described by Whitehead in 1997 [16]. For this purpose the program PEST 4 will be used. The recommendation on the continuation will be based on: (1) stopping rules as described above; and (2) the most recent information from medical literature or congresses in the field of cerebrovascular disease.

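### The 712/750 sample size is a single-look figure with no allowance for the sequential testing to which the plan also assigns 80% power; at the planned 712 evaluable patients that power is slightly missed

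*Protocol article*

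**What the plan says.** In the protocol article, the Power calculation section sets out these inputs:

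- Effect: "Assuming an absolute increase of 10% of favourable outcome at 90 days by additional IA therapy".
- Control rate: "a presumed incidence of the primary outcome event of 30% in the group treated with optimal medical care".
- Error rates: "This calculation was based on a type 1 error of 5%, a type 2 error of 20" per cent.
- Result: "we calculated that 712 patients would be needed".
- Method: "The sample size formula used originated from the standard work on clinical trials by SJ Pocock". No sequential adjustment is mentioned.
- Recruitment target: "To account for potential dropout a target of 750 patients was set". No other purpose is given for the extra 38 patients.

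The Monitoring section describes a symmetrical two-sided stopping rule for efficacy and says that the trial's size rests on the same 10-point assumption. The first interim analysis comes when 10 patients have 3-month data, and the data go to the DSMB every 4 months after that. The operating characteristics are given as follows: "A restricted procedure will be used with alpha equal to 0.05 and a power of 0.80". PEST 4 is named as the software.

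**The concern.** Two sections attach the same 5% error rate, the same 80% power and the same 10-point effect to two different tests. One is a single test at the end. The other is a sequence of tests, any of which may end the trial.

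With the overall type 1 error held at 5%, no repeated test can have more power at a given maximum size than the single test on the full data. If some of the 5% is spent at earlier looks, the maximum size must rise to keep 80% power. The article's only margin above the single-look size is already assigned to dropout.

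If recruitment ends at 750 and about 5% are lost, the sequential design therefore falls short of its stated power. If the boundary is followed to its own maximum, the trial may run beyond its stated size. The article does not say which. In a trial that could end without crossing a boundary, readers and the DSMB should know the power it really had.

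**Working it through.** **1. Reproduce 712.** Inputs from Power calculation: p1 = 0.30, p2 = 0.40, type 1 error 5%, power 80%. Equal allocation is assumed: the article says that "patients will be randomised into one of the two treatment arms" but gives no ratio. The test is taken as two-sided, because a one-sided test would give 562.

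Pooled-variance formula, with mean rate 0.35:

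n per arm = [1.960 × √(2 × 0.35 × 0.65) + 0.8416 × √(0.21 + 0.24)]² / 0.10² = (1.3221 + 0.5646)² / 0.01 = 355.9, so 356 per arm and **712** in total.

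The short form with the multiplier rounded to 7.9 agrees: (0.21 + 0.24) / 0.01 × 7.9 = 355.5, again 356. Single-look power at 356 per arm is 0.8001.

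The stated confidence interval is also a single-look figure. The standard error of the log risk ratio at 356 per arm is √(0.7/(0.3 × 356) + 0.6/(0.4 × 356)) = 0.1038. Then 1.333 × exp(±1.96 × 0.1038) gives 1.09 to 1.63, as printed.

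**2. The margin.** 750 − 712 = 38, and 1 − 712/750 = 5.07%. All of it is assigned to dropout.

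**3. Add the sequential test.** The article gives neither the boundary shape nor the number of looks, so both are assumptions here. The boundary on the score statistic is ±(a + cV), where V is information. The constant a is solved numerically so that overall two-sided alpha is 0.05 over equally spaced looks. A slope c of zero is the flat boundary, the mildest of the shapes considered. R is the ratio of the maximum size to the single-look size at 80% power.

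Flat boundary:

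| Looks | R | Maximum evaluable for 80% | Recruited at 5.07% dropout | Power, 712 evaluable | Power, 750 evaluable |
|---|---|---|---|---|---|
| 5 | 1.028 | 733 | 772 | 78.9% | 80.9% |
| 10 | 1.040 | 741 | 780 | 78.4% | 80.5% |
| 20 | 1.047 | 746 | 786 | 78.1% | 80.2% |
| Continuous | 1.057 | 753 | 793 | 77.8% | 79.9% |

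The evaluable column is 712 × R and the recruited column is 750 × R, with unrounded R and rounded up.

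**4. Sensitivity to slope.** Slopes are expressed as a fraction of the design effect, with 5 to 20 looks.

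| Slope | Power, 712 evaluable | Power, 750 evaluable | R |
|---|---|---|---|
| One quarter | 76.2–77.2% | 78.3–79.2% | 1.07–1.10 |
| One half | 71.9–72.9% | 73.9–74.9% | 1.21–1.24 |

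These rows show the direction and possible size of the effect. They do not describe the trial's actual boundary, which is not given.

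**The case against.** **Size of the loss.** The strongest reply is that the loss is small. With a flat boundary it is 1 to 2 points at 712 evaluable and disappears if all 750 are evaluable. The 5% is a planning allowance, the analysis is by intention to treat, and the Monitoring section promises active follow-up of 90-day data. This limits the severity. It does not remove the inconsistency, because the plan itself assigns the 38 patients to dropout and cannot spend them twice.

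**The stronger reading.** A reader might infer that 750 patients cannot deliver 80% power, or that power is as low as 72%. The documents support neither. Complete follow-up with a flat boundary gives about 80–81% at 5 to 20 looks, and the lower figures need a slope that the article never states.

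**Missing boundary details.** The slope, number of looks and maximum information may stand in the full protocol. A journal article may leave them there, and their absence is not the point. The point is that the stated figures do not fit together.

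**Target, not a cap.** The article calls 750 a target and does not exclude an overrun. A restricted procedure run to its own maximum would keep its 80%, but 750 would then not be the size that provides it.

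**Unadjusted final test.** The Data analysis section mentions only a risk ratio with a 95% confidence interval. If that decided the trial whatever the boundary, power would not fall, but the overall 5% type 1 error would no longer be assured.

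**Conclusion.** The point stands in a limited form. That 712 is a fixed-sample number, and that the step to 750 covers dropout only, follows from the article without any assumption beyond equal allocation and a two-sided test. That a sequential procedure with the same alpha and power needs a larger maximum holds for any boundary that spends error at interim looks. So the stated 80% is not reached at the planned 712 evaluable patients.

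The size is less certain. For a flat boundary and 5 to 20 looks, the shortfall is about 1 to 2 points, equivalent to roughly 21 to 34 evaluable patients (733 − 712 and 746 − 712). A sloped boundary would make it larger, by an amount that cannot be fixed from the article. This should be fixed, but it does not threaten the validity of the trial.

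**What to change.** Keep the target of 750. For the restricted procedure actually programmed in PEST 4, compute the maximum information and the power at 750 recruited with the planned dropout of about 5%. Then restate the power in both Power calculation and Monitoring so that they agree. The figure will be below 80%: about 78–79% if the boundary is flat, and lower if it is sloped. Add a sentence saying that 712 is the single-look size and that the sequential design's power is reported separately.

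The cost is one run of software that the plan already names and a slightly less favourable stated power. No patients are added. With 21 patients randomised by July 2013, according to the Trial status section, the correction would come early.

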#### Data analysis

Continuous data will be summarised with means and standard deviations. For count data percentages will be given.

The primary aim of the univariable analysis is to compare the proportion of patients with a favourable outcome at 90 days between the two treatment groups. For this purpose a risk ratio with corresponding 95% CI will be calculated. The analyses will be based on the intention-to-treat principle.

Multivariable analyses will only be carried out if important incomparability is detected between the two treatment groups. In that case risk ratios will be calculated that are adjusted for the variables that show baseline imbalance. To this end Poisson regression will be used, similar to that used in the BASICS registry study [2].

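### The primary risk ratio and 95% CI are not tied to the sequential stopping rule, so an unadjusted interval could decide significance and overstate the effect after an early stop

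*Protocol article*

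**What the plan says.** Three sections of the Protocol article bear on this.

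- **Data analysis.** The proportions with a favourable outcome at 90 days are compared by intention to treat: "For this purpose a risk ratio with corresponding 95% CI will be calculated". The section does not mention interim looks, a boundary or an adjusted interval.
- **Monitoring.** The efficacy rule is symmetrical and two-sided: "A restricted procedure will be used with alpha equal to 0.05 and a power of 0.80". The first look comes when 10 patients have 3-month data. After that, "Every 4 months thereafter the DSMB will be given the latest follow-up data". The method is Whitehead's and the software is PEST 4.
- **Power calculation.** "Assuming an absolute increase of 10% of favourable outcome at 90 days by additional IA therapy", with "a presumed incidence of the primary outcome event of 30% in the group treated with optimal medical care", "we calculated that 712 patients would be needed". The section then gives the result expected on these assumptions: a risk ratio of 1.33 with 95% CI 1.09 to 1.63. The target was then raised: "To account for potential dropout a target of 750 patients was set".

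**The concern.** The article contains two ways to read the same primary outcome and does not say which one decides. A sequential test that holds 5% overall needs a critical value above 1.96 at the last look. An ordinary 95% CI corresponds to 1.96. The interval can therefore exclude 1 in a trial whose boundary was never crossed.

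Estimation is affected as well. A trial that stops for benefit tends to stop on a high fluctuation, so the conventional risk ratio at that moment is biased away from 1. The stopping rule makes early stopping likely if the design effect is true, so this would be the usual case.

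**Working it through.** **1. The plan's own figures.** Inputs from Power calculation: 30% against 40%, 5% error, 80% power. Two-sided testing and 1:1 allocation are inferred, because together they reproduce the stated size.

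Per arm, n = [1.960·√(2·0.35·0.65) + 0.842·√(0.30·0.70 + 0.40·0.60)]² / 0.10² = (1.322 + 0.565)² / 0.01 ≈ 356, so the total is 712, as stated. The unpooled formula with the factor rounded to 7.9 gives 0.45/0.01 × 7.9 = 355.5, also 356 per arm.

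**2. What kind of interval is 1.09 to 1.63?** The standard error of ln RR at 356 per arm is √(0.7/(0.3·356) + 0.6/(0.4·356)) = √(0.00655 + 0.00421) = 0.1038. Then 1.333 × exp(±1.96 × 0.1038) gives 1.09 and 1.63. This is the ordinary interval for a trial with a single analysis at 712.

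**3. Simulation with an O'Brien-Fleming-like shape.** 100,000 binomial trials per setting; first look at 10 patients; 6, 10, 16, 25 or 40 equally spaced looks; maximum 712 or 750. With n per arm and t and c favourable outcomes, S = (t − c)/2 and V = n·p̄(1 − p̄)/2. The trial stops when |S| > a·√Vmax, with a set so that the overall two-sided error is at most 5%. This gave a = 2.05 to 2.15, which is also roughly the critical value at the last look. At stopping, or at the end, the unadjusted interval is ln RR ± 1.96·√(1/t − 1/n + 1/c − 1/n).

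| Quantity | Result over all settings |
|---|---|
| No effect: boundary crossed | 4.2–5.0% |
| No effect: unadjusted CI excludes 1 | 5.5–6.1% |
| True RR 1.33: trial stops early | 62–80% |
| True RR 1.33: median RR after early stop for benefit | 1.41–1.45 |
| True RR 1.33: median RR over all trials | about 1.36 |
| True RR 1.33: coverage of unadjusted CI | 94.3–94.8% |

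Take the settings where the boundary uses almost the full 5%. At 712 patients, 10 looks give 4.97% against 5.87%, and 40 looks give 4.97% against 6.08%. The excess is 0.9 to 1.1 points.

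With true RR 1.33, every trial that crossed the boundary also had a CI excluding 1. Disagreement is therefore the difference between the two rates, for example 81.5% and 83.8% (750 patients, 40 looks), or 2.3 points. Over all settings it is 0.7 to 2.4 points.

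**4. Sensitivity to the shape.** A second simulation, again with 6 to 40 looks, calibrated both shapes to 5%.

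| Quantity | O'Brien-Fleming shape | Constant boundary |
|---|---|---|
| No effect: unadjusted CI excludes 1 | 5.8–6.1% | 7.6–7.9% |
| True RR 1.33: median RR after early stop for benefit | 1.42–1.44 | 1.51–1.53 |

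About 60 to 76% of trials with true RR 1.33 stopped early for benefit. At 19 looks, the boundary was not crossed while the unadjusted CI excluded 1 in 2.6% of such trials (O'Brien-Fleming shape) or 15% (constant).

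**5. Sensitivity to the number of looks.** The registry's more than 600 patients in 5 years is about 10 a month, or 40 per look, and 750/40 is about 19 looks. Trial status reports 21 patients from October 2011 to July 2013, about one a month, which would mean far more looks. This hardly matters. In a Brownian-motion calculation with 5 to 60 looks, the error from reading 1.96 at the end was 5.7 to 6.1% for the O'Brien-Fleming shape and 7.5 to 8.3% for the constant one.

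**The case against.** The Data analysis section nowhere calls its interval unadjusted, and it gives no rule that success means an interval excluding 1. The interval in Power calculation is a planning illustration. Monitoring names an established sequential method and its software, and a condensed article may leave the terminal analysis to the full protocol or analysis plan, which are not shown. Some exaggeration after an early stop occurs in any sequential trial.

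Much of this stands. That the interval is conventional is an inference. It has support, because the only interval the article shows as its expected result is the fixed-sample one, and nothing in the article points to an adjusted one. The point is therefore more than missing detail: the stated primary analysis, read with the article's own illustration, does not fit its stopping rule.

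A reader might also infer that looking every 4 months pushes the error above 5%. The article does not support that. Monitoring fixes 0.05 for the whole procedure, and the simulated boundary stays at 4.2 to 5.0%. Testing at 1.96 at every look without a boundary would give 19 to 33%, but this is not planned. Nor should the constant-boundary figures be read as the trial's own. Nothing in the article suggests that shape, and they mark only an assumed upper end.

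**Conclusion.** The concern holds as a mismatch between sections, not as a failure of error control. The sequential rule keeps the 5%. Only if the unadjusted interval decides significance does the error rise, to about 6% with an O'Brien-Fleming-like boundary and at most about 8% with a constant one.

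The larger effect is on the estimate. If the true relative increase is 33%, a trial stopped early for benefit would typically report 42 to 44%, or somewhat over 50% under the constant boundary. Over all trials the distortion is small (median about 1.36) and coverage stays close to 95%.

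These sizes rest on assumed boundary shapes, 6 to 40 equally spaced looks and 1:1 allocation. They leave out stopping on outside evidence, which Monitoring also allows and which no boundary covers. The weight is moderate: it should be clarified, but it does not invalidate the design.

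**What to change.** Add to Data analysis, or to the analysis plan if it is not already there:

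- Significance for the primary outcome is judged only by the sequential boundary described under Monitoring.
- The primary p-value, risk ratio and 95% CI come from the terminal analysis that matches the sequential design, for example a median-unbiased estimate with an adjusted CI, and include patients whose outcomes arrive after the stopping decision.
- The conventional risk ratio and CI are reported alongside as supplementary figures.
- The interval in Power calculation is labelled as a fixed-sample illustration.

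The cost is a few sentences. No extra patients or data are needed, and the sequential method already planned supports such an analysis. The price is a slightly wider interval and a slightly less favourable estimate after an early stop for benefit.
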